## Study Withdrawal/Discontinuation

A participant can withdraw from the study at any time by verbalizing or writing to the investigators as a request to discontinue participation. All data collected from the participant until withdrawal will be kept in our records.

## Ethical Considerations

Ethics approval: We will seek the approval of the VUMC institutional review board before conducting the study.

Protocol modifications: The PI will report any update on study protocol or deviations in practice to the IRB, and study recruitment will be halted before IRB approval.

Declaration of interests: The PI has no relevant financial or non-financial conflicts of interest to disclose.

Authorship eligibility: Authorship will be granted based on the criteria of the International Committee of Medical Journal Editors, and we will not involve professional writers in any study-related communication or disseminated documents.

## Statistical Considerations

Sample size: Since we do not have prior data in this patient cohort to appropriately power or simulate our analysis, we used the mean and standard deviation of SDM-Q-9 in the literature [86.7 ( $\pm 11.6$ )]. To ensure that this study has adequate power to detect a clinically meaningful effect size and provide data for future studies, we assume a 5% risk of type I error and a 20% risk of type II error, a 1:1 enrollment ratio, and a targeted increase of 3 times the minimal clinically important difference ( $4^{17}$ ). This means that 20 patients needed to be allocated to each arm. Since this intervention has not been utilized in colorectal patients before, we target an expected rejection rate of 50%, meaning 80 patients should be approached (40 in each arm).

Data analysis plan: Patient characteristics will be compared between the 3D-printed model and standard care arms with the chi-squared test for categorical variables and the Student's t-test for comparisons between continuous variables. The postintervention SDM-Q-9, the preintervention and postintervention STAI-6, and the Patient Education Assessment Questionnaire scores will be compared between the study arms using the restricted maximum-likelihood estimation to account for the intraclass differences. The postintervention score will be treated as a dependent variable, while the preintervention score will be treated as a covariate. A similar subgroup analysis will be conducted after dichotomizing health literacy into adequate (17-20) and inadequate or marginal ( $<17$ ) groups. The level of significance will be at  $\alpha = 0.05$  throughout the manuscript. Statistical analyses will be performed using Stata (version 17, StataCorp LLC, College Station, TX). We do not plan on conducting any interim analysis.

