## Trial Design

We will conduct a single-center pilot cluster randomized control superiority trial. Participating surgeons will be randomly assigned to either the control arm (standard care) or the intervention arm (3D-printed model) using the opaque sealed envelope method. Patients will be recruited in a cluster and study cohort, depending on the next available surgeon. A 1:1 enrollment ratio will be targeted (Figure 5). Blinding will not be performed.

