## Patient Participation / Enrollment

Six consenting colorectal surgeons will be randomly assigned to study arms (standard care vs. intervention) using the opaque sealed envelope method by the research nurse. All consenting patients who meet the inclusion criteria will be assigned to the next available surgeon by personnel unrelated to this study. Patients will then be asked to complete preoperative questionnaires (as per protocol) to measure baseline anxiety levels (STAI-6) and current medical knowledge (Patient Education Assessment). Following, one group will receive traditional education from their physician using 2D images, whereas the other patient cohort will receive the same education but with a 3D printed model (Figure 6). Subsequently, both groups will take the SDM-Q-9 questionnaire and retake the STAI-6 and Patient Education Assessment surveys (Figure 5). **There will be no subject randomization in this study.** Participant enrolment, assignment to study arms, and cluster randomization will be performed by persons unrelated to the research. The cluster randomization method will be used to prevent the mixing and contamination of the intervention. This study will be conducted per the current version of the Declaration of Helsinki and in agreement with the International Conference on Harmonization guidelines on Good Clinical Practice.

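### The sample size states no allowance for clustering by six surgeons, 20 per arm does not follow from its own inputs, and 80% power holds only for a small ICC with the number of clusters ignored

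*Protocol*

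**What the plan says.** The Trial Design section reads "We will conduct a single-center pilot cluster randomized control superiority trial". Under Patient Participation / Enrollment, "Six consenting colorectal surgeons will be randomly assigned to study arms", and the same section rules out randomising individual patients.

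The sample-size paragraph under Statistical Considerations lists these inputs:

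- For the mean and SD, "we used the mean and standard deviation of SDM-Q-9 in the literature", given as 86.7 and 11.6.
- The errors and ratio: "we assume a 5% risk of type I error and a 20% risk of type II error, a 1:1 enrollment ratio".
- The effect: "a targeted increase of 3 times the minimal clinically important difference", with that minimal difference given as 4, so 12 points.

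It concludes: "This means that 20 patients needed to be allocated to each arm". A 50% refusal rate then raises the number to approach to 40 per arm, 80 in all. The paragraph presents the study as adequately powered, while conceding that no prior data in this population exist to power or simulate the analysis. The data analysis plan in the same section compares scores by restricted maximum likelihood (REML) to allow for intraclass differences.

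**The concern.** The design and the analysis both recognise clustering by surgeon, but the calculation between them states nothing about it. Within-surgeon correlation is plausible for this outcome: all nine SDM-Q-9 items in the Appendix ask about the doctor's conduct or about the decision reached with the doctor, so patients of one surgeon rate the same communicator.

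Clustering costs power in two ways. Correlated patients carry less information than the same number of independent ones. And with six randomised units, the between-surgeon variance behind the treatment comparison is estimated on few degrees of freedom.

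The type II error is a fixed statement in this protocol, not a detail deferred to a later plan. If it is too favourable, a non-significant SDM-Q-9 result could be given more weight than the design can bear.

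**Working it through.** **Inputs from the protocol.** SD 11.6; difference 3 × 4 = 12; type I error 5%; power 80%; 1:1 ratio; 20 per arm; six surgeons.

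**Assumptions.** Two-sided test (sidedness is not stated); 11.6 taken as the total SD; three surgeons per arm (the text says only that six are assigned), so m = 20/3 = 6.67 patients per surgeon, of equal size; ICC from 0 to 0.20, because the protocol gives none.

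**Step 1: the protocol's own figure.** For independent patients, n per arm = 2 × (1.960 + 0.842)² × 11.6² / 12² = 14.7, so 15. The t-test version gives 16 (power 78% at 15, 81% at 16). A one-sided test needs 12 by the normal formula. The stated 20 does not reproduce. Twenty independent patients per arm would give 91% power (normal) or 89% (t, 38 df).

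Twenty does appear with inputs the protocol does not state: 90% power by the normal approximation, a two-sided 2.5% level with a t-test, or a design effect of 20/16 = 1.25 to 20/15 = 1.33, which implies an ICC of about 0.044 to 0.059 (0.064 if the unrounded 14.7 is used). The step from 20 to 40 per arm, 20/(1 − 0.5), does reproduce.

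**Step 2: add clustering.** Design effect DE = 1 + (m − 1) × ICC = 1 + 5.67 × ICC. Standard error SE = 11.6 × √(2 × DE/20). Noncentrality = 12/SE. Power is computed with the normal critical value, and from the noncentral t on 6 surgeons − 2 arms = 4 df. The 95% half-width on 4 df is 2.776 × SE.

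| ICC (assumed) | DE | Effective n per arm | SE | Power, normal | Power, 4 df | 95% CI half-width, 4 df |
|---|---|---|---|---|---|---|
| 0 | 1.00 | 20.0 | 3.67 | 91% | 69% | 10.2 |
| 0.05 | 1.28 | 15.6 | 4.16 | 82% | 59% | 11.5 |
| 0.10 | 1.57 | 12.8 | 4.59 | 74% | 51% | 12.7 |
| 0.20 | 2.13 | 9.4 | 5.36 | 61% | 40% | 14.9 |

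**Step 3: break-even.** With the normal critical value, 80% power needs 12/SE = 2.80, so DE = 20/14.67 = 1.363 and ICC = 0.363/5.67 = 0.064. With t on 38 df the break-even ICC is 0.052. On 4 df there is none: power is below 80% even at ICC 0.

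**Step 4: the planned type of analysis.** In a simulation of REML estimation for this layout, a z test gave power of 85%, 82%, 78% and 72% at ICC 0, 0.02, 0.05 and 0.10. Its type I error was 6.4% at ICC 0.05 and 7.9% at 0.10, so part of that power comes from exceeding the 5% level. Satterthwaite-type degrees of freedom gave 70%, 60% and 52% at ICC 0, 0.05 and 0.10, close to the 4-df column.

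**The case against.** A reader might infer that the calculation treats patients as independent and that 80% power is simply not delivered. The protocol supports neither in that form.

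On the first, independent patients would need 15 or 16 per arm, not 20. The four or five extra match a modest design effect, so an unstated clustering allowance cannot be excluded; nor can 90% power or a stricter level. What can be said is that no allowance is stated and the number is not reproducible.

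On the second, the shortfall depends on an ICC that the protocol does not give and on the degrees of freedom. With large-sample inference and an ICC of 0.05 or below, the design-effect calculation keeps 80%. The protocol plans a REML model, not a surgeon-level t-test, and the degrees-of-freedom method is commonly left to the statistical analysis plan. It would therefore be too strong to quote a 40% to 60% chance of missing the target without conditions: that range comes only from the 4-df test at ICC 0.05 to 0.20. At ICC 0 the 4-df test misses 31%, and the normal approximation misses 18%, 26% and 39% at ICC 0.05, 0.10 and 0.20.

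It is also fair to say that the protocol calls the trial a pilot, admits the lack of prior data and intends to inform later studies. This tempers the point without removing it: the same paragraph still claims adequate power and commits to "a 20% risk of type II error", and neither the pilot label nor a REML analysis supplies that power.

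**Conclusion.** The point holds in conditional form. The protocol attaches an unqualified type II error to a six-cluster trial with no stated clustering allowance, and its patient number exceeds what its inputs yield (20 against 15 to 16 per arm). The claimed power is right only if the ICC is about 0.05 to 0.06 or less and the small number of clusters is ignored. With inference that respects six clusters, it is about 69% at best and falls to 51% at ICC 0.10 and 40% at 0.20. At ICC 0.10 and above, the 4-df half-width exceeds the 12-point target itself.

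These sizes rest on three surgeons per arm, equal numbers per surgeon, a total SD of 11.6, a two-sided 5% test and ICC values that are assumptions. Unequal surgeon volumes would tend to lower the power further.

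**What to change.** Keep the 40 patients and rewrite the sample-size paragraph:

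1. State how 20 per arm was reached (sidedness, power, any design effect), or correct it.
2. Replace the unqualified 20% type II error with a short table of power and 95% CI half-width at ICC 0, 0.05, 0.10 and 0.20. Name the assumed surgeons per arm, patients per surgeon, SD and degrees of freedom. The half-widths on 4 df are 10.2, 11.5, 12.7 and 14.9 points.
3. Say that a non-significant result from this pilot is not evidence of no effect.
4. Do not claim that the trial will estimate the ICC precisely: six surgeons cannot do so.

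The cost is one paragraph of wording and a less favourable stated power. No patients are added, and neither the randomisation nor the planned model has to change.

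### The printed sample-size inputs give 15 or 16 patients per arm, not 20, and the step to 20 is not stated

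*Protocol*

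**What the plan says.** Everything is in the sample-size paragraph of the protocol's Statistical Considerations. It takes the mean and standard deviation of the SDM-Q-9 from a published study (86.7, SD 11.6) and sets the target at three times a minimal clinically important difference of 4. On error rates and allocation it says: "we assume a 5% risk of type I error and a 20% risk of type II error, a 1:1 enrollment ratio". It then states the result as following from these inputs: "This means that 20 patients needed to be allocated to each arm". Only after that does it apply a 50% rejection rate, which takes 20 per arm to 40 approached per arm, 80 in all.

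The data analysis paragraph in the same section adds: "The level of significance will be at $\alpha = 0.05$ throughout the manuscript". Neither paragraph says whether testing is one- or two-sided. The sample-size paragraph mentions no design effect, ICC, attrition allowance or division of alpha. Yet Trial Design and Patient Participation / Enrollment describe a cluster trial that randomises six surgeons, and Outcome Measurements lists two primary outcomes.

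**The concern.** The protocol prints a complete set of inputs for a two-sample comparison of means, then a number that those inputs do not produce. This is not a detail that a statistical analysis plan could supply: input and result stand next to each other and disagree.

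The paragraph says the study should also provide data for future studies, and the trial is called a pilot. Planners of the next trial need to know whether 20 already contains an allowance for clustering or for something else. As printed, they cannot tell. Some may credit the surplus over 16 to clustering, for which the text gives no basis.

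**Working it through.** **Inputs from the protocol (Statistical Considerations).** SD σ = 11.6; difference δ = 3 × 4 = 12; type I error 0.05; type II error 0.20, so power 0.80; 1:1 allocation.

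**Assumed.** Two-sided testing, with one-sided shown as well. For the clustering illustration: three of the six surgeons in each arm and equal caseloads, so 20/3 = 6.67 patients per surgeon.

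**1. Trying to reproduce the printed 20.** Per arm, n = 2(z₁₋α/₂ + z₁₋β)²σ²/δ².

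- Two-sided, normal: 2 × (1.960 + 0.842)² × 134.56/144 = 14.67, so 15.
- Two-sided, exact t-test: 15 per arm gives power 0.781 and 16 gives 0.808, so 16.
- One-sided: 12 (normal) or 13 (t-test).

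None of these is 20. The two-sided shortfall is 4 to 5 patients per arm: 20/16 = 1.25 and 20/15 = 1.33.

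**2. Does the rejection rate explain it?** No. It is applied to the 20: 20/(1 − 0.5) = 40 per arm, 80 in total. That step is correct. Starting from 15 or 16 it would give 30 or 32 per arm, 60 or 64 in total.

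**3. Unstated inputs that would reach 20.**

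| Unstated input | Result per arm |
|---|---|
| 90% power | 2 × (1.960 + 1.282)² × 134.56/144 = 19.64, so 20 (normal); 21 (t-test) |
| Two-sided alpha 0.025 for two primary outcomes | 18 (normal); 20 (t-test) |
| 20% attrition added to 16 | 16/0.8 = 20 |
| Design effect of 1.25 (on 16) to 1.36 (on 14.67) | 20 |
| Rounding up | 20 |

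Under the assumed 6.67 patients per surgeon, the design effects correspond to an ICC of 0.25/5.67 = 0.044 up to 0.363/5.67 = 0.064. Several routes arrive at 20, and the protocol points to none of them.

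**4. Power at 20 per arm, ignoring clustering.** The standardised difference is 12/(11.6 × √(2/20)) = 3.27. Power is Φ(3.27 − 1.96) = 0.905 by the normal approximation and 0.890 by the t-test.

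**5. Illustration with clustering.** Design effect DE = 1 + (6.67 − 1) × ICC; noncentrality 3.27/√DE; two-sided 5% cluster-level t-test on 6 − 2 = 4 degrees of freedom. The ICCs are assumed.

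| ICC | DE | Power |
|---|---|---|
| 0 | 1.000 | 0.69 |
| 0.02 | 1.113 | 0.65 |
| 0.05 | 1.283 | 0.59 |
| 0.064 | 1.363 | 0.56 |
| 0.10 | 1.567 | 0.51 |

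The row at 0.064 is instructive. That ICC returns 20 per arm at 80% power in the simple design-effect formula, but with six surgeons and 4 degrees of freedom the power is about 56%.

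**The case against.** The best defence is that the discrepancy is harmless. For independent patients 20 exceeds the need, the trial is a pilot, and the later step from 20 to 80 approached is right. This stands in part: the direction is conservative under independence, and nothing in enrolment has to change. It does not make the printed derivation true, and the surplus is no reassurance in a trial that randomises six surgeons.

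Sidedness is also unstated, so the two-sided result is an assumption. That is fair, but the one-sided result of 12 or 13 lies further from 20.

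A reader might draw two stronger conclusions that the protocol does not support:

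- **That 20 reveals 90% power or a hidden design effect.** Both fit numerically, but so do an alpha split, attrition and rounding. The 90% match also holds only for the normal approximation, since the t-test needs 21. Any choice among these is conjecture.
- **That the trial is overpowered, at 89% to 90%.** Those figures treat patients as independent. Surgeons are the randomised units, the planned analysis allows for intraclass differences, and the illustration gives clearly lower power.

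**Conclusion.** The point holds as an arithmetic inconsistency. The printed inputs give 15 or 16 per arm with two-sided testing assumed, and fewer if one-sided, so the stated 20 does not follow from them. Which unstated input was used, if any, cannot be determined from the protocol.

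The independence-based power of 89% to 90% only measures the mismatch with the stated 80%; it says nothing reliable about this design. The range of 69% to 51% for ICCs of 0 to 0.10 is itself an illustration. It rests on a 3:3 split of surgeons, equal caseloads and a cluster-level test, none of which the protocol states. This is a reporting correction worth making, not evidence that the enrolment target should be lowered.

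**What to change.** Rewrite the sample-size sentence in three parts:

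1. State the sidedness, and say that the printed inputs give 15 (normal) or 16 (t-test) per arm under independent sampling if the test is two-sided.
2. Either name the additional input actually used to reach 20, with its value, or say that 20 was chosen on other grounds for a pilot.
3. Report the power at 20 per arm under randomisation of six surgeons, over a range of assumed ICCs, with the surgeon split and caseloads stated.

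An ICC or type II error should not be picked afterwards because it returns 20; that would fit an input to the answer. The cost is a few sentences and a short power table, with no change to the numbers enrolled or approached.

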## Outcome Measurements

**Primary Outcome Measures:** The difference in the levels of shared decision-making using the validated SDM-Q-9 questionnaire (Figure 1) and the differential change in anxiety levels post-intervention using the validated STAI-6 questionnaire (Figure 2).

**Secondary Outcome Measures:** A differential change in the patient knowledge level captured by our 13-question Patient Education Assessment survey (Figure 3) and evaluating if the change is consistent when categorized by health literacy scores based on the BRIEF: Health Literacy Screening Tool (Figure 4).

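### REML is the only stated safeguard for clustering by six surgeons, and no small-sample reference distribution is named; a normal-based test would run at about 6% to 11%, not 5%, for ICCs of 0.05 to 0.30

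*Protocol*

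**What the plan says.** The Trial Design section calls this a "single-center pilot cluster randomized control superiority trial". Under Patient Participation / Enrollment, "Six consenting colorectal surgeons will be randomly assigned to study arms", and individual patients are not randomised. Outcome Measurements names two primary outcomes: "The difference in the levels of shared decision-making using the validated SDM-Q-9 questionnaire" and "the differential change in anxiety levels post-intervention using the validated STAI-6 questionnaire".

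Under Statistical Considerations, the scores "will be compared between the study arms using the restricted maximum-likelihood estimation to account for the intraclass differences", with the post-consultation score as the response and the pre-consultation score as a covariate. Significance is set at 0.05 and the software is Stata 17. For the sample size, "we assume a 5% risk of type I error and a 20% risk of type II error". The section does not name the test statistic for the arm effect, its degrees of freedom or a small-sample adjustment.

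For baseline data, "Patient characteristics will be compared between the 3D-printed model and standard care arms with the chi-squared test for categorical variables", and Student's t-test is used for continuous variables. Neither test is adjusted for surgeon.

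**The concern.** REML is a way of estimating variance components. It reduces their bias, but it does not say which distribution the estimated arm effect should be compared with. In a trial with many clusters this matters little, because t and normal critical values nearly coincide. With six clusters split 3:3 there are 6 − 2 = 4 between-surgeon degrees of freedom, and the two-sided 5% critical value is 2.78 rather than 1.96.

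There is a second difficulty. A between-surgeon variance estimated from so few surgeons often comes out at zero. The fitted model then treats patients as independent, although surgeons were the units randomised.

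At stake is whether a significant result on either primary outcome could be merely a difference between two sets of three surgeons, declared more often than the 5% that the protocol claims.

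**Working it through.** **Inputs from the protocol.** Six surgeons; 20 patients per arm, so 20/3 ≈ 6.7 per surgeon; SDM-Q-9 SD 11.6; target difference 3 × 4 = 12 points; alpha 0.05; power 80%.

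**Assumptions.** The split is 3:3 (inferred from the 1:1 enrolment target; the protocol gives no split of surgeons). Tests are two-sided (sidedness is not stated). The ICC is not given, so 0 to 0.30 is taken as a range.

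**The plan's own figure.** n per arm = 2(1.960 + 0.842)² × (11.6/12)² = 14.7, so 15 (16 with the exact t). The stated 20 does not follow from 80% power. It is the normal-approximation answer for 90% power: 2(1.960 + 1.282)² × (11.6/12)² = 19.6. Neither calculation contains a design effect. This is a separate matter, but it bears on the power figures below.

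**Type I error.** Take m = 7 patients per surgeon and no arm effect. Let MSB be the between-surgeon mean square within arm (4 df) and MSW the within-surgeon mean square (36 df).

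- REML surgeon variance = max(0, (MSB − MSW)/m).
- SE of the arm difference = √(2V/(3m)), where V = MSB if MSB > MSW, and otherwise V = (4 MSB + 36 MSW)/40.
- REML with normal reference: reject if |difference/SE| > 1.96.
- Surgeon-level t-test: V = MSB always; reject above 2.776.
- Chance of a zero variance estimate = P(F(4,36) < 1/(1 + 7·ICC/(1 − ICC))). At ICC 0.05 the bound is 0.731, at 0.10 it is 0.5625 and at 0.20 it is 0.364.

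| ICC | REML, normal | REML, t on 4 df | Surgeon-level t, 4 df | Surgeon variance estimated as zero |
|---|---|---|---|---|
| 0 | 4.3% | 0.6% | 5.0% | 58% |
| 0.02 | 5.2% | 0.8% | 5.0% | 51% |
| 0.05 | 6.4% | 1.2% | 5.0% | 42% |
| 0.10 | 8.0% | 1.9% | 5.0% | 31% |
| 0.20 | 10.0% | 3.1% | 5.0% | 17% |
| 0.30 | 11.0% | 3.9% | 5.0% | 9% |

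Rejection rates are simulated, with at least 400,000 runs per ICC; repeat runs differ by about 0.1 percentage point. The normal-reference test passes 5% at an ICC of about 0.015. Its ceiling is P(|t₄| > 1.96) = 12.2%.

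**Check at the planned 40 patients.** REML was fitted numerically (4,000 runs each) with a normal reference and ICC 0.10. With 7, 7 and 6 patients per surgeon in each arm, the error is 8.1% without a covariate (as for SDM-Q-9) and 7.8% with a baseline covariate (as for STAI-6). With unequal loads (12, 5, 3 against 10, 7, 3) it is 9.3% and 9.2%.

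**Power of a 4-df test, 20 per arm, 12 points.** Design effect = 1 + (20/3 − 1)·ICC. SE = 11.6 × √(0.1 × design effect). Power comes from the noncentral t with noncentrality 12/SE.

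| ICC | Design effect | SE | Noncentrality | Power |
|---|---|---|---|---|
| 0 | 1.00 | 3.67 | 3.27 | 69% |
| 0.05 | 1.28 | 4.16 | 2.89 | 59% |
| 0.10 | 1.57 | 4.59 | 2.61 | 51% |
| 0.20 | 2.13 | 5.36 | 2.24 | 40% |

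**Baseline tests.** A patient-level t-test on a characteristic that varies by surgeon rejects 5.0%, 8.6%, 12.4% and 19.5% at ICC 0, 0.05, 0.10 and 0.20.

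**The case against.** The protocol recognises clustering, and it does not say that a normal reference will be used or that a correction will be left out. A degrees-of-freedom method is often left to a statistical analysis plan, and none is shown here. A reader might infer that the planned tests are inflated as they stand. The documents do not support that. Inflation needs both a normal reference and an ICC above about 0.015, and the protocol states neither. At ICC 0 the normal-based test is slightly below 5%, and REML referred to t on 4 df is conservative at every ICC examined. This part of the objection stands, and the point is therefore conditional.

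It does not remove the point. The section sets out estimator, covariate, subgroup cut-offs, alpha and software, and offers REML as the whole remedy for clustering. With 4 degrees of freedom the reference distribution determines whether the stated 5% holds. The pilot label does not settle the matter either, since the trial is also described as a superiority trial with a stated error rate.

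On baseline data, a reader might infer that the tests will produce false imbalance. Patients go to the next available surgeon, and nothing in the protocol shows that their characteristics cluster by surgeon. These tests also have no bearing on the primary error rate. The baseline point is therefore minor.

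**Conclusion.** The concern holds in conditional form. The protocol relies on REML alone with six randomised surgeons and does not fix a small-sample reference. Tested against the normal distribution, the primary comparisons would run at about 6% to 11% for ICCs of 0.05 to 0.30, and in many such trials the surgeon variance would be estimated as zero. The result rests on the assumed 3:3 split, two-sided testing, near-equal surgeon loads (unequal loads gave somewhat higher rates at ICC 0.10) and an assumed ICC range. It does not show that the trial's error rate is in fact inflated, because the reference distribution is unstated.

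**What to change.** Make the primary test a comparison of surgeon means by a t-test on 4 degrees of freedom. SDM-Q-9 is given only after the consultation, so its means are unadjusted; STAI-6 and knowledge can be adjusted for the pre-consultation score.

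Alternatively, fit REML with a surgeon random intercept, name the small-sample degrees-of-freedom method, and state in advance what is done when the surgeon variance is estimated as zero. Only t on 4 df was examined above for REML; any other method should be checked by simulation at this size before it is adopted.

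Base the confidence interval on the same test and report the ICC. Show baseline data descriptively by arm, without p-values.

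The change in wording is small, but it has a price: wider confidence intervals and, for the 12-point target with 20 per arm, power of about 69% at ICC 0 falling to about 40% at ICC 0.20. The 80% power statement should be restated accordingly.

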## Study Procedures and Data Collection

Recruitment: Surgical patients presenting to the colorectal clinic of a tertiary care hospital will be recruited during their preoperative visit.

Informed Consent: Patients who agree to participate in the study will be assessed to confirm eligibility and given a consent form from a clinic nurse or study investigator. All study-related questions will be answered before they agree to sign the written informed consent document, which will be recorded in the Research Electronic Data Capture (REDCap) database.

Study Visit: Surgical patients will be asked to complete the study questionnaires before their preoperative consultation (STAI-6 and Patient Education Assessment) before their consultation and SDM-Q-9, STAI-6, and Patient Education Assessment after the consultation at their preoperative consultation. These patients will only participate in the study during this visit and will not require any follow-up.

SDM-Q-9: This is a validated, nine-item self-report survey that measures how involved patients feel in the decision-making process with their healthcare provider . This survey will only be administered once, post-consultation (Figure 1).

STAI-6: This validated six-item tool  will be used to measure the patient's anxiety levels before and after the preoperative consultation to establish a baseline and understand how each intervention affects anxiety levels (Figure 2).

Patient Education Assessment: The 13-question survey aims to assess patients' knowledge and understanding of their colon anatomy, disease, procedure, and complication risks. This survey will be given both before and after informed consent to assess any changes (Figure 3).

The baseline demographic and clinical information of each patient will be collected by the research nurse at the preoperative visit, recorded in the institutional REDCap database, and compared between the study arms.

REDCap Data Entry: This project will utilize the REDCap electronic data capture tools hosted at Vanderbilt University Medical Center for data collection and management. REDCap will be used to capture all recruited patients who are enrolled in the study and store their individual data as well as study consent documentation.

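### The baseline-covariate rule cannot apply to SDM-Q-9, so this primary outcome gets no baseline adjustment although usable baseline scores are collected

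*Protocol*

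**What the plan says.** The protocol's Outcome Measurements section puts SDM-Q-9 first among the primary outcomes: "The difference in the levels of shared decision-making using the validated SDM-Q-9 questionnaire". Study Procedures and Data Collection says of this instrument: "This survey will only be administered once, post-consultation (Figure 1". The same section, and Patient Participation / Enrollment, place STAI-6 and the Patient Education Assessment before the consultation as well as after it.

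The data analysis plan under Statistical Considerations covers all three scores in one sentence: "The postintervention SDM-Q-9, the preintervention and postintervention STAI-6, and the Patient Education Assessment Questionnaire scores will be compared between the study arms". For all of them that sentence plans REML, to allow for clustering. The covariate rule follows: "The postintervention score will be treated as a dependent variable, while the preintervention score will be treated as a covariate". No other covariate is named. BRIEF appears only in dichotomised form, for a subgroup analysis.

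For baseline data the plan says: "Patient characteristics will be compared between the 3D-printed model and standard care arms with the chi-squared test for categorical variables". Continuous variables get Student's t-test. Only the six surgeons are randomised; on patients the protocol states: "There will be no subject randomization in this study".

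**The concern.** The rule follows a list that includes SDM-Q-9, yet it needs a measurement that SDM-Q-9 does not have. The analysis of a primary outcome is thus either impossible as written or, on a kinder reading, has no baseline covariate. Meanwhile two baseline scores from the same patients are used only for their own follow-up scores.

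Two things are at stake. The first is precision, in a trial with about 40 patients and six clusters. The second is exposure to chance differences between arms, which are larger when few surgeons are randomised. There is also a procedural risk: if the SDM-Q-9 model is left open in an unblinded trial, covariates could be chosen after the data are seen. Finally, the baseline tests treat patients as independent, while the outcome analysis in the same paragraph does not.

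**Working it through.** **Reading the text.** The plan's list gives SDM-Q-9 as post-intervention only and STAI-6 as pre and post. Read literally, the rule cannot be carried out for SDM-Q-9. Read narrowly, as covering only scales that have a pre score, it leaves SDM-Q-9 with no covariate. Both readings give the same model: arm plus surgeon clustering under REML.

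**The plan's own figure.** Statistical Considerations gives an SD of 11.6, a target of 3 × 4 = 12 points, 5% type I error, 80% power and 20 patients per arm. Two-sided, n = 2 × (1.960 + 0.842)² × 11.6² / 12² = 14.7, so 15 per arm, or 16 with the t-test. The stated inputs do not reproduce 20. At 20 per arm, power is 89% (t-test) if clustering is ignored. This does not affect the covariate question, and I take 20 per arm as the planned size.

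**Gain from adjustment.** The protocol gives no ICC, no correlation of any baseline score with SDM-Q-9, and no number of surgeons per arm. Assumptions: three surgeons per arm (inferred from six surgeons and the 1:1 target), ICC 0.01 to 0.20, and covariates that explain R² = 0.10 or 0.25 of patient-level variance and none of the surgeon-level variance.

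Variance of the arm difference = 2 × [ICC × 11.6²/3 + (1 − ICC) × 11.6² × (1 − R²)/20]. Power is from the noncentral t with 6 − 2 = 4 df.

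At ICC 0.05, 11.6² = 134.56 splits into 6.73 between surgeons and 127.83 within:
- R² = 0: 2 × (2.243 + 6.392) = 17.27, SE 4.16, power 58.8%
- R² = 0.10: 2 × (2.243 + 5.752) = 15.99, SE 4.00, power 62.0%
- R² = 0.25: 2 × (2.243 + 4.794) = 14.07, SE 3.75, power 67.2%

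| Assumed ICC | No covariate | R² = 0.10 | R² = 0.25 |
|---|---|---|---|
| 0.01 | 66.8% | 70.8% | 77.5% |
| 0.05 | 58.8% | 62.0% | 67.2% |
| 0.10 | 51.0% | 53.3% | 57.0% |
| 0.20 | 40.2% | 41.5% | 43.5% |

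The gain is about 4 to 11 percentage points at ICC 0.01 and 1 to 3 at ICC 0.20. The few clusters cost more: with 4 df and no covariate, power is 69% even at ICC 0.

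**Chance imbalance.** For a baseline variable with its own ICC, the SD of the standardised arm difference is √(2 × DE/20), with DE = 1 + (20/3 − 1) × ICC. At ICC 0 and 0.20 this is 0.316 and 0.462. The probability of a difference above 0.25 SD is then 43% and 59%. If the variable correlates 0.3 with SDM-Q-9 (assumed), an imbalance of one such SD moves the SDM-Q-9 difference by 0.3 × 0.316 × 11.6 = 1.1 to 0.3 × 0.462 × 11.6 = 1.6 points. The MCID is 4 and the target is 12.

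**Baseline tests.** At characteristic ICCs of 0.05, 0.10 and 0.20 (assumed), DE is 1.28, 1.57 and 2.13. A nominal 5% test that ignores clustering rejects with probability 2 × [1 − Φ(1.96/√DE)], about 8%, 12% and 18% by normal approximation.

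**The case against.** The best defence is that the plan labels SDM-Q-9 as post-intervention only, so the next sentence is naturally read as applying where a pre score exists, and a covariate list may stand in an SAP that is not shown. The first part is fair: this need not be called a contradiction. The second is fair as far as it goes, since a missing list alone would be no finding. But the protocol does fix a covariate rule, and that rule yields nothing for a primary outcome while suitable baseline data are at hand.

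Stronger readings are tempting, and the documents do not support them:

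- A reader might infer that SDM-Q-9 is compared with no adjustment at all. REML for surgeon clustering is planned for it.
- A reader might infer that the estimate is biased, or that case mix differs by surgeon. Leaving out covariates does not by itself bias a randomised comparison. Patients go to the next available surgeon, assigned by personnel outside the study. This limits selection, though it does not exclude it.
- A reader might take the whole surgeon-level gap as the harm. Its SD is √(2/3) × √ICC × 11.6 = 2.1, 3.0 and 4.2 points at ICC 0.05, 0.10 and 0.20. That gap comes from having few clusters and would exist however the covariate sentence were worded. SDM-Q-9 items rate what the doctor did, so much of it may be surgeon style, which patient-level covariates cannot remove.
- A reader might call the baselines prognostic. No section links any of them to SDM-Q-9. Aim 3 only asks whether health literacy affects it.

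Two practical limits stand. The protocol does not fix when BRIEF is completed. The baseline questionnaires come after assignment to a surgeon in an unblinded trial, so they precede the consultation but not the allocation. On baseline tests, the plan lets nothing depend on them, so their harm is limited to misleading p-values.

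**Conclusion.** The point holds in a limited form. The only covariate rule in the protocol cannot serve SDM-Q-9, and this primary outcome is left with surgeon clustering but no baseline covariate, although baseline STAI-6 and knowledge scores are collected. At ICC 0.05, adjustment would lift power for 12 points from about 59% to 62-67%, with a modest reduction in exposure to chance imbalance. This rests on an assumed ICC, an assumed R² of 10-25%, an inferred three surgeons per arm, and 4 df. It is an improvement worth making because it is nearly free. It does not show that the planned comparison is invalid, and it does not repair the weakness of having six clusters.

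**What to change.** Write separate rules for the outcomes before outcome data are seen:

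- STAI-6 and the Patient Education Assessment: post score as outcome, own pre score as covariate, clustering by surgeon as planned.
- SDM-Q-9: a linear mixed model with a surgeon random intercept, adjusted for baseline STAI-6 and baseline Patient Education Assessment score. Add BRIEF as a continuous score only if its completion before the consultation is written into the procedures.
- Baseline balance: report standardised differences between arms in place of chi-squared and t-test p-values, and do not choose covariates from observed imbalance.

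The cost is a few sentences and no new measurement. The model spends two patient-level degrees of freedom, or three with BRIEF, out of roughly 40 − 6 = 34. If the baselines turn out to be unrelated to SDM-Q-9, that small loss is the whole downside.
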